- H2: Cortical activation measured by fNIRS from the visuomotor integration and the attentional network areas during the baseline phase will be lower in the children with DCD than in children with TD. Relative activation levels ( $[O_2Hb]$ ) in both networks during adaptation and consolidation will demonstrate opposite profiles in children with DCD (start low, end high) vs children with TD (start high and end low). In addition, acute intense exercise will narrow, but may not completely close, the gap between children with DCD who receive the exercise intervention and children with TD controls.
- H3: In a pilot study, combining fDCS technology that measures  $CMRO_2$  and rCBF with fNIRS technology will provide us with the possibility to obtain more accurate and robust information of the children's brain activity during learning than using fNIRS alone.

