## **OBJECTIVES**

Although the long term objective of this line of research will address the underlying mechanisms of acute exercise effects on motor learning and possible brain activity changes with developmental coordination disorder (DCD), we currently defined the specific objectives of this project as follows:

- O1. To study the acute intense exercise effects on the motor learning (adaptation and consolidation) in children with and without DCD from a behavioral perspective (performance and execution).
  - O1.1- Characterize the possible motor learning modulators (physical fitness; physical activity level; attentional and cognitive capabilities) in children with and without DCD.
  - O1.2- Compare the motor learning (adaptation and consolidation) ability of children with and without DCD while performing a rotational visuo-motor task (rVMA) (CON-DCD vs. CON-TD).
  - O1.3- Examine the effect of acute intense exercise on motor learning (adaptation and consolidation) while performing a rotational visuo-motor task in children with and without DCD.
- O2. To explore cortical activation in the visuomotor integration and the attentional network areas while learning a motor adaptation task in children with and without DCD under rest or post-exercise conditions. Visuomotor integration and attentional network areas will include dorsolateral pre-frontal cortex (DLPFC), ventrolateral pre-frontal cortex (VLPFC), and oculo pre-frontal cortex (OPFC).
  - O2.1- Assess changes in cortical activation ([O2Hb]) during rVMA learning (adaptation and consolidation) in children typically developed and in children with DCD.
  - O2.2- Evaluate the impact of acute intense exercise on changes in cortical activation ([O2Hb]) during rVMA learning (adaptation and consolidation) in children typically developed and in children with DCD.
  - O2.3- Associate the presence of changes in the cortical activation variables with differences shown in behavioral variables.
- O3: To explore via a pilot study the combined use of two optical neuroimaging techniques (fNIRS and fDCS) to measure cortical activation in the visuomotor integration and the attentional network areas while learning a motor adaptation task in children with and without DCD under rest or post-exercise conditions.
  - O3.1- Evaluate the usability of the hybrid device

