  - O3.2- Assess the potential to obtain new relevant information of the hybrid device in comparison with using on technology (fNIRS or fDCS) alone.

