The Brite MKII is a portable wave continuous system developed to measure concentration changes of oxyhemoglobin ( $[O_2Hb]$ ) and deoxyhemoglobin ( $[HHb]$ ), which indirectly reflect brain activity. The light sources (optodes) transmit two wavelengths,  $\pm 760$  nm and  $\pm 850$  nm, and the receiver is a high sensitive PIN diode with ambient light protection. The distance between the receiver and the optodes and the sensitive PIN diode and the intensity of the light can be modified to better adjust to participant characteristics. Spring-loaded grommets will be used to improve data quality in dark thick hair. Data acquisition sampling rate will be set to 10 Hz. Oxysoft software (v6.0, Artinis Medical Systems, Netherlands) will allow real time assessment of the quality of the fNIRS signals and zero baseline will be set when acceptable signal-to-noise ratio was obtained. In the pilot study, fDCS will measure cerebral metabolic rate of oxygen extraction ( $CMRO_2$ ), and microvascular cerebral blood flow (CBF) during all motor task phases to assess short and long-term changes in cortical processing. Data acquisition sampling rate of the hybrid device (fNIRS and fDCS) will be set at the same frequency when they collect data together. fNIRS and fDCS data will be analyzed using programs wrote by our team and our collaborators in ICFO.

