We will compare the mean baseline value for each rVMA and brain hemodynamics variables with ANOVAs to evaluate baseline performance across the four groups. Differences between the CON-DCD and CON-TD children groups (O1.2 and O2.1) on the motor learning (adaptation and retention phases) will be explored using independent t-tests in the adaptation set, while 2 (Group) x 3 (Time) ANOVAs with repeated measures will be used to analyze differences in the retention phases. Focusing on the effects of exercise (O1.3 and O2.2), possible differences in the adaptation set will be contrasted by 2 (Group) x 2 (Exercise) ANOVAs and retention tests will be analyzed by 2 (Group) x 2 (Exercise) x 3 (Time) ANOVAs with repeated measures. Association of the changes in brain activation variables with changes occurred in the rVMA variables will be explored using bivariate correlations and multivariate correlations (O2.3). Usability and additional information provided by fNIRS and fDCS will be evaluated qualitatively and contrasted brain activity levels obtained from both technologies using t-test and ANOVAs (adaptation: t-test (Technology); retention tests: 2 (Technology) x 3 (Time) ANOVAs) (O3).

Before any statistical test normality distribution will be tested for all variables via exploration of histograms, Q-Q plots and with the Shapiro-Wilk's normality test. When the normality assumption failed, variable transformation or non-parametric alternative tests will be adequately conducted. In all ANOVAs Greenhouse-Geisser sphericity-corrected values will be used when appropriate. Variables with initial group differences and significantly correlated with the dependent variable will be considered as potential covariates in the ANOVA analyses. Bonferroni *post hoc* analyses will be performed if significant differences are found. In addition, the effect size will be calculated using  $\eta^2p$  (0.01 small, 0.06 medium, 0.14 large effect). Statistical significance was set at  $p < 0.05$  for all analyses.

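### The Technology t-test and ANOVA planned for O3 compare fNIRS levels with fDCS levels, and so cannot show whether the hybrid device is more informative than fNIRS alone

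*Protocol*

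**What the plan says.** H3 (Justification and hypotheses) states that adding fDCS to fNIRS "will provide us with the possibility to obtain more accurate and robust information of the children's brain activity during learning than using fNIRS alone". O3 is worded as exploration: "To explore via a pilot study the combined use of two optical neuroimaging techniques (fNIRS and fDCS"). Its second sub-objective, O3.2, is "Assess the potential to obtain new relevant information of the hybrid device in comparison with using on technology (fNIRS or fDCS) alone". O3.1 concerns usability.

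The Statistical analysis section gives two components for O3:

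- a qualitative one: "Usability and additional information provided by fNIRS and fDCS will be evaluated qualitatively";
- an inferential one: "contrasted brain activity levels obtained from both technologies using t-test and ANOVAs (adaptation: t-test (Technology); retention tests: 2 (Technology) x 3 (Time) ANOVAs").

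On what is measured, the optical neuroimaging section says the fNIRS instrument was "developed to measure concentration changes of oxyhemoglobin" and deoxyhaemoglobin, and that "fDCS will measure cerebral metabolic rate of oxygen extraction" and microvascular cerebral blood flow (CBF). The Variables section defines activation as a rise in [O2Hb], CMRO2 and CBF but a fall in [HHb]. Data reduction normalises each signal to the child's own resting values and gives no scale common to the two technologies. Participants sets the pilot at 10 children from each of four groups and adds that the number depends on development of the device. The two devices record simultaneously in the same child.

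**The concern.** The question and the test do not match, in two ways.

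First, the comparison is the wrong one. H3 and O3.2 set the hybrid against a single technology. The planned factor, Technology, sets fNIRS against fDCS. No analysis places fNIRS plus fDCS beside fNIRS alone, and no measure of accuracy or robustness is tested.

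Second, the levels being contrasted are different physiological quantities. A Technology effect says that one quantity changed more than another. It does not say whether the second quantity carries anything that the first lacks.

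At stake is the interpretation of the pilot. The section sets the 0.05 level for all analyses, so these tests will yield p-values under an objective that they cannot address, while the component that does address it (the qualitative one) has no criterion.

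**Working it through.** The protocol gives no sample size, power or effect size for O3, so there is no figure of its own to reproduce. The check is of logic, followed by illustrations whose parameters are assumed.

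**1. Question against test**

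| Element | What is compared |
|---|---|
| H3 | fNIRS + fDCS against fNIRS alone |
| O3.2 | hybrid against either technology alone |
| Planned t-test (adaptation) | fNIRS level against fDCS level |
| Planned 2 x 3 ANOVA (retention) | fNIRS level against fDCS level, by time |

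Neither planned test matches H3 or O3.2.

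**2. Are the levels comparable?** There are two fNIRS variables ([O2Hb], [HHb]) and two fDCS variables (CBF, CMRO2), so 2 x 2 = 4 pairings could each be called the Technology contrast. In the two pairings with [HHb], the protocol's own definition of activation predicts opposite signs, so a difference is expected whenever the cortex is active. In the two with [O2Hb], both signals should rise. Normalisation to rest might make them unitless (its form is not stated), but the contrast would still be one of response size.

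**3. Can the test separate redundancy from added information?** Simulation, n = 40 paired children, 3,000 runs, two-sided 0.05. In both scenarios the fNIRS signal is f = 0.5 + 0.5x, with x standard normal, and the behavioural outcome y has standard normal error e.

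- *Scenario A, fDCS redundant:* fDCS signal = 1.5f + noise (SD 0.1); y = x + e.
- *Scenario B, fDCS complementary:* fDCS signal = 0.5 + 0.5u, with u independent of x; y = 0.5x + 0.7u + e.

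| Scenario | Technology paired t-test significant | Test of fDCS added to fNIRS significant |
|---|---|---|
| A: no added information | 99.97% | 4.5% |
| B: independent information, same mean | 4.8% | 97.7% |

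The planned contrast points the wrong way in both.

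**4. How often would the contrast be significant for reasons unrelated to added value?** For a difference of d standard deviations and within-child correlation r, the standardised paired difference is dz = d / √(2(1 − r)). With d = 0.5 and r = 0.5, dz = 0.5 / √1 = 0.5. Power of the paired t-test, two-sided 0.05:

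| d, r (assumed) | dz | n = 40 | n = 20 |
|---|---|---|---|
| 0.5, 0.2 | 0.40 | 68% | 39% |
| 0.5, 0.5 | 0.50 | 87% | 56% |
| 0.5, 0.8 | 0.79 | 99.8% | 92% |

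At n = 40 a smaller dz of 0.2 gives 23%, and 0.3 gives 46%. The document fixes none of these inputs.

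**5. Would an R-squared increment with a bootstrap interval be a sound replacement?** No. In-sample R-squared cannot fall when predictors are added. With n = 40, one informative predictor and two pure-noise predictors standing in for CBF and CMRO2, a 95% percentile bootstrap interval for the increase lay above zero in all 300 runs (mean increase about 0.04). The nested-model F-test rejected in about 4 to 6% of runs, close to its nominal 5%.

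**The case against.** The strongest reply is that O3 does not rest on these tests. The sentence that introduces them first assigns usability and additional information to qualitative evaluation, and the wording of O3, O3.2 and H3 is modest: exploring, assessing potential, a possibility. The pilot's size depends on the device and no power is claimed. All of this stands. It limits the weight of the point, but it does not make the Technology contrast relevant to H3.

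A second reply is that the Technology x Time term describes whether the two signals follow different profiles across the retention tests. That is a fair descriptive use and a reason not to insist on deletion. Different profiles are still not a measure of accuracy, robustness or added value.

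A third is that the exact test belongs in a statistical analysis plan. Here the protocol names the tests and their factors, so it has already fixed them.

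Three stronger readings are tempting, and the document does not support them:

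- *That O3 is decided by the t-test and ANOVA alone.* The qualitative evaluation rules this out.
- *That a significant Technology effect will be declared a success for the hybrid.* No such decision rule is stated. It is only a risk of misreading.
- *That the tests will be run unpaired.* The O3 t-test is not labelled independent, as t-tests elsewhere in the section are, and simultaneous recording is stated. The form is simply not named.

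**Conclusion.** The point holds in a limited form. Apart from a qualitative evaluation without criteria, the only inferential analysis named for O3 contrasts the levels of different physiological quantities. Its result, significant or not, is no evidence on whether the hybrid is more informative than fNIRS alone. This conclusion follows from the protocol's own definitions and needs no numerical assumption.

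The numbers only illustrate it. The simulated rates depend on the chosen parameters. The 87% depends on an assumed 0.5 SD difference, a correlation of 0.5 and all 40 children being recorded; it falls to about 56% with 20. Because O3 is an exploratory pilot and O1 and O2 do not use these tests, the consequence is a misdirected pilot analysis, not a threat to the main aims. It should be corrected, since correction is cheap and can be made before the data are analysed.

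**What to change.** Change the O3 analysis wording as follows.

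- **Technology tests.** Remove them as evidence for H3 and O3.2. If they are kept, label them descriptive, name the variables being paired, and analyse them as paired within child.
- **H3 and O3.2.** Compare nested models of a behavioural outcome such as IDE: fNIRS variables alone against fNIRS variables plus CBF and CMRO2, both adjusted for the four pilot groups. Use the nested-model F-test or the cross-validated change in prediction error, not a bootstrap interval for in-sample R-squared.
- **O3.1.** Report the proportion of usable recordings for each technology with a 95% confidence interval. Contrast-to-noise for each signal may be added descriptively. It is again fNIRS beside fDCS, so it does not test H3.
- **Presentation.** Report all of this as exploratory estimation in up to 40 children.

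The cost is a little more analysis on the same children and recordings. The estimates will be imprecise. With an intercept, three group terms, two fNIRS and two fDCS variables, the larger model has 1 + 3 + 2 + 2 = 8 parameters, leaving 40 − 8 = 32 residual degrees of freedom, or 12 if only 20 children are recorded.

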## Ethic treatment

All the procedures of the present research project will be conducted according to the latest revision of the Helsinki Declaration. In addition, this research project has been sent to the Ethics Committee of the Consell Català de l'Esport for its approval.

Previous research has examined the effect of exercise on human cognition and how individual characteristics as fitness level, age, and gender could moderate the exercise effects on cognition. V. Labelle et al. (2014) found that exercise effects on cognition were not moderated by gender. Studies where exercise has been observed to stimulate motor learning in children included male and female in the groups (Lundby et al., 2017; Ferrer-[name] et al., 2018). Therefore, during the execution of this research no distinction for sex or ethnic characteristics will be made during participant recruitment. Yet, a greater number of male participants is expected because DCD has shown greater prevalence in male than female children. More male DCD probable cases are expected in the present study, compared to female DCD cases. Therefore, gender balance across groups may or may not be accomplished in this project. Despite no gender differences were expected, we will introduce sex as covariate in the statistical procedures to better know if any sex effect occurred. Dissemination and transfer of the research will be take care to high standards preserving the gender dimension explaining similarities and differences if any. To do so we will be assisted by our colleague in INEFC [name] and her group of research (<https://inefcgiseafe.com/>) who are highly recognized by their research and work about the gender dimension. All participants recruited during the study will provide verbal and written assent (see Annex 4) along with their guardian's written consent (see Annex 3). As stated in the assent and consent formularies, participants will be free to quit the study in any moment if they don't want to continue participating.

Treatment of the data will follow the current normative. Department of the Presidency of the Generalitat of Catalonia data management delegate ([https://presidencia.gencat.cat/ca/el\\_departament/proteccio-dades/delegat-da-de-proteccio-de-dades/](https://presidencia.gencat.cat/ca/el_departament/proteccio-dades/delegat-da-de-proteccio-de-dades/)) will be request and a data management plan will be elaborate using DMPonline platform (<https://dmp.csuc.cat/>) to ensure data protection and their proper use. Participants' personal information will always be kept safe in order to preserve their anonymity. That is, participants' identity information will only be stored in a unique safe file and afterwards participants identity will be codified though all data registration and treatment procedures.

Lastly, a supervisor will be designated in each school in order to oversee that all study procedures are performed according to this ethics declaration. In addition, the school supervisor will be requested to provide support to the researchers in case of accident or injury of the participants during the experimental procedure, providing assistance with the emergency protocols of the school. The school supervisor will also be the mediator between researchers and participants/participants' guardians in any case of necessity.

A list of the principal tasks related to the research objectives are presented indicating members of the group involved. Critical tasks that could alter the expected timing (underlined) are related to the accessibility of the sample and DCD children detection.

- **Task 1.** Participant recruitment
  - Task1.1. Participant recruitment. Investigators involved: PI1, WT3, WT4. Duration: M1-36.
- **Task 2.** Objective 1
  - Task 2.1. Collection of participant's characterization data, including: Health status (PARQ), physical activity engagement (PAQ-C), academic and daily living activities performance (MABC-2 checklist), possible comorbidities report, regular medication intakes, possible psychosocial problems (Conners CBRS), exclusion criteria related-data, and the family-related information. Investigators involved: PI1, PI2, WT3. Duration: M2-40.

- Task 2.2. Intelligence quotient data collection using the Test of on-verbal intelligence version 4 (TONI-4). Investigators involved: PI1, PI2, WT3. Duration: M2-40.
- Task 2.3. Motor coordination data collection using the Movement assessment battery for children – second edition (MABC-2). Investigators involved: PI1, PI2, WT3. Duration: M2-40.
- Task 2.4. Participant's anthropometric data collection. Investigators involved: PI1, PI2, WT3. Duration: M2-40.
- Task 2.5. Estimation of participant's VO2max via the 20-meter shuttle run test (20mSRT). Investigators involved: PI1, PI2, WT3. Duration: M2-40.
- Task 2.6 Exercise intervention execution and motor learning (rotational visuomotor adaptation task) behavioral data collection. Investigators involved: PI1, PI2, RT1, WT3, WT4. Duration: M2-40.
- Task 2.7. Reduce data and carry bio-statistical procedures. Investigators involved: PI1, PI2, RT1, WT1, WT2, WT3. Duration: M7-45.
- Task 2.8. Produce results and disseminate according to dissemination plan. Investigators involved: PI1, PI2, RT1, WT1, WT2, WT3. Duration: M14-48.
- **Task 3.** Objective 2 and 3
  - Task 3.1. Brain activity data acquisition under resting state and baseline execution of the motor task (rotational visuomotor adaptation task without deviation of hand movements). Investigators involved: PI1, RT1, WT3, WT4. Duration: M2-40.
  - Task 3.2. Brain activity data collection during the acquisition and retention of the new motor skill (rotational visuomotor adaptation task with hand movements deviated 60 degrees clockwise). Investigators involved: PI1, PI2, RT1, WT3, WT4. Duration: M2-40.
  - Task 3.3. Reduce data and carry bio-statistical procedures. Investigators involved: PI1, PI2, RT1, WT1, WT2, WT4. Duration: M7-45.
  - Task 3.4. Produce results and disseminate according to dissemination plan. Investigators involved: PI1, PI2, RT1, WT1, WT2, WT3, WT4. Duration: M14-48.
- **Task 4.** Return to society and preparation of future projects
  - Task 4.1. Development of DCD awareness booklets/brochures and website. Investigators involved: PI1, PI2, RT1, WT1, WT2, WT3. Duration: M1-4 (phase 1) and M42-48 (phase 2).
  - Task 4.2. Workshops to increase knowledge about DCD between parents and educators. Investigators involved: PI1, RT1, WT1, WT3. Duration: M1-4 (phase 1) and M42-48 (phase 2).
  - Task 4.3. Define methodological procedures and prepare documentation for future projects. Investigators involved: PI1, PI2, RT1, WT1, WT2, WT3, WT4. Duration: M43-48.

Given the large sample needed for this project and the total number of sessions that each participant will be engaged in, we estimate that data collection would last 39 months approximately (school vacations periods included). Therefore, we elaborated a work plan schedule of 4 years (Figure 4).

#### Figure 4. Deliverables and chronogram

##### Deliverables:

- D1, M2: Report on protocols.
- D2, M12: Preliminary test of optical systems.
- D3, M12: Project status report.
- D4, M24: Update on data acquisition and recruitment.
- D5, M24: Project status report.
- D6, M36: Subject recruitment status and summary statistics.
- D7, M36: Project status report.
- D8, M40: Update on completed tasks.
- D9, M48: Report on outreach and future planning.
- D10, M48: Final project report.

*Note: Deliverables are for internal management purposes and for evaluating the ongoing research timing.*

| Workpackage and tasks |                                        | YEAR 1 |   |   |   |   |   |   |   |   |    |    |    | YEAR 2 |    |    |    |    |    |    |    |    |    |    |    | YEAR 3 |    |    |    |    |    |    |    |    |    |    |    | YEAR 4 |    |    |    |    |    |    |    |    |    |    |    |  |
|-----------------------|----------------------------------------|--------|---|---|---|---|---|---|---|---|----|----|----|--------|----|----|----|----|----|----|----|----|----|----|----|--------|----|----|----|----|----|----|----|----|----|----|----|--------|----|----|----|----|----|----|----|----|----|----|----|--|
| 1                     | Recruitment                            | 1      | 2 | 3 | 4 | 5 | 6 | 7 | 8 | 9 | 10 | 11 | 12 | 13     | 14 | 15 | 16 | 17 | 18 | 19 | 20 | 21 | 22 | 23 | 24 | 25     | 26 | 27 | 28 | 29 | 30 | 31 | 32 | 33 | 34 | 35 | 36 | 37     | 38 | 39 | 40 | 41 | 42 | 43 | 44 | 45 | 46 | 47 | 48 |  |
| 1.1                   | Participant recruitment                |        |   |   |   |   |   |   |   |   |    |    |    |        |    |    |    |    |    |    |    |    |    |    |    |        |    |    |    |    |    |    |    |    |    |    |    |        |    |    |    |    |    |    |    |    |    |    |    |  |
| 2                     | Screening of participants              |        |   |   |   |   |   |   |   |   |    |    |    |        |    |    |    |    |    |    |    |    |    |    |    |        |    |    |    |    |    |    |    |    |    |    |    |        |    |    |    |    |    |    |    |    |    |    |    |  |
| 2.1                   | Characterization data                  |        |   |   |   |   |   |   |   |   |    |    |    |        |    |    |    |    |    |    |    |    |    |    |    |        |    |    |    |    |    |    |    |    |    |    |    |        |    |    |    |    |    |    |    |    |    |    |    |  |
| 2.2                   | Intelligence data                      |        |   |   |   |   |   |   |   |   |    |    |    |        |    |    |    |    |    |    |    |    |    |    |    |        |    |    |    |    |    |    |    |    |    |    |    |        |    |    |    |    |    |    |    |    |    |    |    |  |
| 2.3                   | Motor development data                 |        |   |   |   |   |   |   |   |   |    |    |    |        |    |    |    |    |    |    |    |    |    |    |    |        |    |    |    |    |    |    |    |    |    |    |    |        |    |    |    |    |    |    |    |    |    |    |    |  |
| 2.4                   | Anthropometric data                    |        |   |   |   |   |   |   |   |   |    |    |    |        |    |    |    |    |    |    |    |    |    |    |    |        |    |    |    |    |    |    |    |    |    |    |    |        |    |    |    |    |    |    |    |    |    |    |    |  |
| 2.5                   | VO2max data                            |        |   |   |   |   |   |   |   |   |    |    |    |        |    |    |    |    |    |    |    |    |    |    |    |        |    |    |    |    |    |    |    |    |    |    |    |        |    |    |    |    |    |    |    |    |    |    |    |  |
| 2.6                   | Exercise intervention                  |        |   |   |   |   |   |   |   |   |    |    |    |        |    |    |    |    |    |    |    |    |    |    |    |        |    |    |    |    |    |    |    |    |    |    |    |        |    |    |    |    |    |    |    |    |    |    |    |  |
| 2.7                   | Data analysis                          |        |   |   |   |   |   |   |   |   |    |    |    |        |    |    |    |    |    |    |    |    |    |    |    |        |    |    |    |    |    |    |    |    |    |    |    |        |    |    |    |    |    |    |    |    |    |    |    |  |
| 2.8                   | Interpretation & dissemination         |        |   |   |   |   |   |   |   |   |    |    |    |        |    |    |    |    |    |    |    |    |    |    |    |        |    |    |    |    |    |    |    |    |    |    |    |        |    |    |    |    |    |    |    |    |    |    |    |  |
| 3                     | Motor learning (VYMA) and neuroimaging |        |   |   |   |   |   |   |   |   |    |    |    |        |    |    |    |    |    |    |    |    |    |    |    |        |    |    |    |    |    |    |    |    |    |    |    |        |    |    |    |    |    |    |    |    |    |    |    |  |
| 3.1                   | In vivo test of fNIRS and SPAD systems |        |   |   |   |   |   |   |   |   |    |    |    |        |    |    |    |    |    |    |    |    |    |    |    |        |    |    |    |    |    |    |    |    |    |    |    |        |    |    |    |    |    |    |    |    |    |    |    |  |
| 3.2                   | Learning sessions with neuroimaging    |        |   |   |   |   |   |   |   |   |    |    |    |        |    |    |    |    |    |    |    |    |    |    |    |        |    |    |    |    |    |    |    |    |    |    |    |        |    |    |    |    |    |    |    |    |    |    |    |  |
| 3.3                   | Data analysis                          |        |   |   |   |   |   |   |   |   |    |    |    |        |    |    |    |    |    |    |    |    |    |    |    |        |    |    |    |    |    |    |    |    |    |    |    |        |    |    |    |    |    |    |    |    |    |    |    |  |
| 3.4                   | Interpretation & dissemination         |        |   |   |   |   |   |   |   |   |    |    |    |        |    |    |    |    |    |    |    |    |    |    |    |        |    |    |    |    |    |    |    |    |    |    |    |        |    |    |    |    |    |    |    |    |    |    |    |  |
| 4                     | Return to society & future             |        |   |   |   |   |   |   |   |   |    |    |    |        |    |    |    |    |    |    |    |    |    |    |    |        |    |    |    |    |    |    |    |    |    |    |    |        |    |    |    |    |    |    |    |    |    |    |    |  |
| 4.1                   | Outreach & awareness materials         |        |   |   |   |   |   |   |   |   |    |    |    |        |    |    |    |    |    |    |    |    |    |    |    |        |    |    |    |    |    |    |    |    |    |    |    |        |    |    |    |    |    |    |    |    |    |    |    |  |
| 4.2                   | Workshop parents/educators             |        |   |   |   |   |   |   |   |   |    |    |    |        |    |    |    |    |    |    |    |    |    |    |    |        |    |    |    |    |    |    |    |    |    |    |    |        |    |    |    |    |    |    |    |    |    |    |    |  |
| 4.3                   | Future planning                        |        |   |   |   |   |   |   |   |   |    |    |    |        |    |    |    |    |    |    |    |    |    |    |    |        |    |    |    |    |    |    |    |    |    |    |    |        |    |    |    |    |    |    |    |    |    |    |    |  |

